#### Criteria for discontinuing or modifying allocated interventions {11b}

Participating schools in the intervention arm will be given the freedom to choose from the flexible menu of active ingredients in the programme and work at the pace that is right for the individual school setting. In line with the PhunkyFoods Logic Model (Additional file 1), schools will be encouraged to participate in active ingredients 1 and 2 within the first 3 months as part of the model fidelity. Whilst the programme pace is led by schools, the EDCs will support and encourage participating schools to consider active ingredient 3 by 6 months of the programme and will highlight opportunities to select ‘Active Ingredients’ 4–8 after 6 months. This flexibility is indicative of the complexity of the trial and hence the theory-based approach to research perspectives and hypotheses which aim to understand the interplay of mechanisms and context in evaluating complex interventions [10].

#### Strategies to improve adherence to interventions {11c}

The PhunkyFoods programme is run by Purely Nutrition. All EDCs are employed by Purely Nutrition and supported with training and guidance on how to implement the programme according to the Programme Manual [13] and the Logic Model, whilst providing the flexibility for schools to work at the pace that is right for their setting. The study will collect data on of how many components each school delivers and this will be included as part of the analysis.

#### Relevant concomitant care permitted or prohibited during the trial {11d}

N/A—no concomitant care is permitted or prohibited as part of this trial.

#### Provisions for post-trial care {30}

N/A—no provisions for ancillary and post-trial care as part of this trial.

### Outcomes {12}

At the time of trial registration, it was thought that the outcome measures would be measured at baseline (T1) and then at 8 months post-intervention delivery (T2), identifying September as the start time of the intervention. However, in recognition that the training phase of the programme delivered in May to July includes active ingredients 1 and 2, it is felt more appropriate to include this phase in the time period from baseline to the final value. Therefore, the outcomes will be measured at baseline (T1) and then 12 months (T2) after the intervention starts, including the initial training for teachers.

#### Primary outcome measures

The primary outcome measures are as follows:Food literacy will be measured by the Tool for Food Literacy Assessment in Children (TFLAC - UK) at baseline (T1) and at 12 months after intervention delivery (T2). The Food Literacy outcome is composite and contains numerical values for food systems knowledge, cooking skills, cooking knowledge, nutrition knowledge and self-efficacy. The original questionnaire developed by Amin et al. [14] Tool for Food Literacy Assessment in Children (TFLAC) was developed by a panel of food and nutrition experts in three phases for content validity, with test-retest reliability and internal consistency assessed amongst children (*n* = 706) aged 9–11 years. Food literacy domain-specific Cronbach alpha values were food systems knowledge (0.80), cooking skills (0.94), cooking knowledge (0.63), nutrition knowledge (0.83) and self-efficacy regarding eating (0.98), and intraclass correlation coefficients were 0.64−0.70 (*P* < 0.001).The TFLAC was adapted for use in the UK by consulting with EDCs at PhunkyFoods during an away day on 10 September 2021. Terminology was changed from US English words to equivalent UK English words and then further checks on the survey language were undertaken by the authors of this protocol. Example changes included ‘measuring cup’ to ‘measuring jug’ and ‘oven mitt’ to ‘oven glove’. No other changes were made to the content, structure, order, or phrasing of questions in the survey design that could have an impact on internal consistency.Cooking skills will be measured by the CooC11 child survey by Dean et al. [15] at baseline (T1) and at 12 months after intervention delivery (T2). CooC11 and CooC7 are two measures of cooking competence developed and reviewed by an expert panel, based on new recommendations about children’s developmental skills and are relevant for this specific age group [15, 16]. The internal consistency reliability of CooC11 was good, with a Cronbach score of 0.86 and a temporal stability rating ICC of 0.91. The measure was shown to be responsive to change in the cooking camp intervention with differences in pre-cooking camp mean (SD) of 21.75 (7.89) to post camp mean of 26.13 (8.89) [15].

#### Secondary outcome measures

The secondary outcome measures are as follows:Total fruit and vegetable intake will be measured using a shortened version of the Child Assessment of Diet Evaluation Tool (CADET) [17] at baseline (T1) and at 12 months after intervention delivery (T2). The CADET is a 24-h food diary that measures the nutritional intake of children and has been validated for use with children aged 3–11 years [17, 18]. A sample of children (*n* = 67) completed the diary with a mean age of 9.3 years in the validation study [17]. The proposed CADET fruit and veg survey uses a sub-section of CADET, which assesses dietary information on fruit and vegetables only. This shortened version was chosen by the authors to make it easier for parents to complete and for the potential of a shorter version to increase the survey return rate.

#### Participant timeline {13}

Participant timeline is presented in Fig. 1.

**Fig. 1 Fig1:**
[figure not shown]
Schedule of enrolment, intervention and assessments

#### Sample size {14}

The study by Dean and colleagues in 2019, based on 469 participants and using CooC11 to assess cooking competence, showed a significant increase (*p* < 0.01) in cooking competence at follow-up after the camp-based intervention compared with results at baseline [15]. The results of CooC11 at baseline (mean (SD)) were 21.75 (7.89) and at follow-up 26.13 (8.89). The difference in cooking competence scores was therefore approximately 5 units, the equivalent of a moderate effect size (Cohen’s *d* = 0.52).

A power calculation was undertaken using STATA based on this moderate effect size of the Dean study. To detect this effect size with a minimum of 90% power and using a 2-level model with individuals clustered within schools (individual schools are being recruited rather than individual children), 13 clusters are needed in each arm. This calculation was based on the assumption that a mean of 15 children would be included in each school, and therefore, 195 children would be needed in each arm. The power is reduced when a large proportion of variation is at the school level (most of the variation will be at the individual level); in other words, children within a school may be more similar to each other than children at another school and therefore a conservative estimate of 20% of variation at the school level was assumed. It is likely that it is less than this, but there is too little information available related to cooking competence to be able to estimate it with more certainty. Due to the reasonable possibility that schools may drop out of the study, we aim to recruit 14 schools per arm (28 schools in total).

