**Methods:**

A cluster randomised controlled trial will be undertaken in 28 primary schools in North Yorkshire, UK, including a total population of children aged 7–9 years (*n* = 420). The trial has two arms: (a) the intervention group receiving PhunkyFoods programme (*n* = 210) and (b) the wait-list control group receiving the usual school curriculum (*n* = 210). The intervention ‘PhunkyFoods’ will be delivered by Purely Nutrition Ltd. The participating school staff are supported with training, policy development and access to resources to improve the delivery of nutrition education. Children participate through whole school assemblies, classroom activities, and after-school clubs about food preparation, cooking healthy meals and healthy living. Schools, parents and children have access to healthy meal recipes through the PhunkyFoods website. The primary outcomes are differences in food literacy and cooking skills scores between control and intervention arms after 12 months of the intervention and adjusted for baseline values. The secondary outcome is differences in fruit and vegetable intake between the arms after 12 months (adjusted for baseline). Treatment effects will be examined using mixed ANOVA and regression analysis. Primary analyses will adjust for baseline food literacy and cooking skills scores and secondary analysis will adjust for pre-specified baseline school and child level covariates.

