### Interventions

#### Explanation for the choice of comparators {6b}

The control group schools will receive their usual existing school curriculum for food science as delivered in the Food Technology schemes of work, without any support from the PhunkyFoods Programme. This may include specific nutritional components, designed and delivered by the school. In the UK, the Department for Public Health sets out the topics that should be covered in Food Technology lessons for primary schools [11] but in reality, this is likely to look different across school settings. We will ensure we collect relevant information on what schools are currently doing in relation to food knowledge and skills and include this information in the analysis as an additional independent variable if deemed appropriate.

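### The target effect in the two-arm power calculation is a before-after change in camp attenders, used as the between-arm difference with no allowance for, or mention of, change in the controls

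*Protocol article*

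**What the plan says.** Section {14} bases the calculation on a study of 469 participants in a cooking camp, which "showed a significant increase (*p* < 0.01) in cooking competence at follow-up after the camp-based intervention compared with results at baseline". It gives CooC11 means (SD) of 21.75 (7.89) before and 26.13 (8.89) after, and continues: "The difference in cooking competence scores was therefore approximately 5 units, the equivalent of a moderate effect size", with Cohen's d given as 0.52. The primary outcome section presents the same pair of means as pre-camp and post-camp scores.

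The same section then uses this effect size in a two-level calculation for at least 90% power. The result is 13 schools per arm, with a mean of 15 children per school (195 per arm) and 20% of the variation at school level. One school per arm is added for dropout, making 14.

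The comparison to be made is between arms. The abstract says: "The primary outcomes are differences in food literacy and cooking skills scores between control and intervention arms after 12 months", adjusted for baseline. Section {20a} fits time and treatment in a mixed ANOVA alongside regression models. Section {6b} describes the comparator: "The control group schools will receive their usual existing school curriculum for food science as delivered in the Food Technology schemes of work". No section gives an expected change in the controls, subtracts one, or argues that it will be zero.

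**The concern.** A before-after change in one group and a difference between two randomised arms are different quantities. The second equals the intervention gain minus the control gain. Controls here are aged 7-9 and are surveyed in March 2022 and again in March 2023. In between they receive usual Food Technology teaching, and they complete the same questionnaire twice. Some rise in their scores is plausible through age, teaching and familiarity with the survey.

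If so, a programme that moved children exactly as far as the camp did would show a between-arm difference smaller than 0.52, and power would be below the stated figure. The background section presents this trial, unlike the feasibility study, as having full power. A null result could therefore be read as good evidence of no worthwhile benefit when the detectable difference was larger than readers supposed.

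**Working it through.** **Inputs from the article.** CooC11 21.75 (7.89) to 26.13 (8.89); d = 0.52; power at least 90%; 13 schools per arm; 15 children per school; school-level share of variance (ICC) 0.20; 1:1 allocation.

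**Assumed.** Two-sided 5%, because {14} states no alpha. Control gains g of 0.5, 1 and 2 units, because the documents give none.

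**1. Origin of d.**
- Difference: 26.13 - 21.75 = 4.38.
- Root-mean-square SD: sqrt((7.89² + 8.89²)/2) = 8.40.
- d = 4.38/8.40 = 0.521, matching the stated 0.52.

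The effect is therefore the before-after change itself. The description as about 5 units rounds 4.38 upward; 5/8.40 would be 0.595.

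**2. The plan's own number of schools.**
- Design effect: 1 + (15 - 1) × 0.20 = 3.8.
- Schools per arm = 2 × (1.960 + 1.282)² × 3.8 / (15 × 0.52²) = 19.7, so 20 rather than 13.
- With 13 schools: effective n = 195/3.8 = 51.3 per arm; standard error of d = sqrt(2/51.3) = 0.197; power = Φ(0.52/0.197 - 1.960) = 75%, or 72% using t with 24 df.
- With 14 schools: 78%.

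The 13 is recovered only with inputs that {14} does not state. Examples are ICC 0.10 (12.4 schools), a baseline correlation of about 0.6 (12.6), or 5 units over the baseline SD of 7.89 (13.3 schools, but then d = 0.63). This shortfall exists at zero control gain and is a separate issue.

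**3. The effect of a control gain alone.** Suppose the design does have exactly 90% power at 4.38 units, however that was reached. By the normal approximation,

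power(g) = Φ(3.2415 × (4.38 - g)/4.38 - 1.960)

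| Assumed control gain (units) | Between-arm difference if the programme matches the camp | Power |
|---|---|---|
| 0 | 4.38 | 90% |
| 0.5 | 3.88 | 82% |
| 1 | 3.38 | 71% |
| 2 | 2.38 | 42% |

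Because the calculation starts from 90%, it does not depend on the ICC or the baseline correlation. Starting instead from 5 units over 7.89, with 13 schools and ICC 0.20, gives 89%, 82%, 73% and 49%: much the same pattern.

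**4. Detectable difference on the stated inputs.** With 13 schools per arm, ICC 0.20 and no credit for baseline adjustment, d for 90% power is 3.2415 × 0.197 = 0.64 (normal), or 0.67 with t. This follows from the cluster arithmetic in step 2 and involves no control gain.

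**The case against.** Power is always conditional on a target. Section {14} names 0.52 as the difference to detect, and using a camp result to choose a moderate target is not in itself an error. A reader might infer that the 90% assumes controls gain nothing. The documents do not support that: the target would also be met if a 12-month programme with eight components outdid the camp by as much as the controls gain. This part of the objection stands. What remains is that the protocol makes neither argument.

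A reader might also infer that the cited study had no control group. The documents do not say. They show only that the figures quoted contain no control change.

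The control gains are assumed, so the power loss is a range and not an estimate. Baseline adjustment is planned and could raise precision: at an assumed correlation of 0.6, 13 schools give about 91% at zero gain, and 83%, 72% and 43% at gains of 0.5, 1 and 2 units. Section {14} claims no such credit, though, and the adjustment reduces variance without turning a before-after change into a between-arm effect. The ICC of 0.20 is described as cautious, which bears on step 2 but not on step 3.

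Finally, {20a} promises effect sizes with measures of variation. That helps in reading a null result but does not correct the stated power.

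**Conclusion.** The mismatch is real and should be corrected in the text. The target of 4.38 units (d = 0.52) is a before-after change standing in for a between-arm difference, no justification is given, and it is probably optimistic. The loss attributable to this point is from 90% to about 82%, 71% or 42% for assumed control gains of 0.5, 1 or 2 units, if the programme only matches the camp.

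Power with 13 schools on the stated inputs would be lower still at those gains. It would be wrong to charge that whole shortfall to this point, because those inputs already give only about 72-75% at zero control gain (two-sided 5%, no baseline adjustment). Nor does the detectable d of 0.64-0.67 show anything about control change. The documents support a target that is weakly justified and likely too large. They do not support a finding that the trial's true power is any one of these figures.

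**What to change.** In {14}:

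- Say that 4.38 units is a before-after change in camp attenders from which no control change has been subtracted.
- Restate power for the between-arm difference, taken as 4.38 minus assumed control gains of 0, 0.5, 1 and 2 units. Show the zero-gain figure so that the choice of target and the number of schools can be judged separately.
- State the alpha and any baseline correlation assumed.
- Give the between-arm difference detectable with 90% power under those inputs (about d = 0.64-0.67 at 13 schools per arm without baseline adjustment).
- Commit to interpreting a non-significant result by its confidence interval against that difference.

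The cost is a few lines and a less favourable stated power. Recruitment, schools and data collection are unchanged.

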#### Recruitment {15}

Eligible schools will be recruited through email, social media, newsletters and follow-up telephone calls. Networks such as North Yorkshire County Council, Huntington Research School and Red Kite Teaching School Alliance will be used to help promote the project in newsletters and social media. Those schools that express an interest in the project will be sent a ‘Cooking in Yorkshire’ Poster, a Headteacher Information Sheet with details about the study, aims and methodology, and invited to a 30-min online school briefing to discuss the project and research design.

Once schools that have received a briefing about the project understand the randomised controlled trial design and data collection elements of the study, they will be asked to sign the Headteacher Consent Form and allocate one class for the research project. Parental and child consent procedures will then take place and have already been outlined early. A flowchart for the trial procedure is shown in Fig. 2.

**Fig. 2 Fig2:**
[figure not shown]
Flowchart of the trial procedures. Children who are in years 3–4 at UK primary schools in Yorkshire are aged 7–9 years

### Assignment of interventions: allocation

#### Sequence generation {16a}

A computer-generated randomisation sequence will be used to allocate schools into the intervention and wait-list control arms of the trial. Block randomisation will be used to ensure equivalence between intervention and waitlist-control schools. Furthermore, schools will be stratified according to region (e.g. Selby or Harrogate) and whether they are above or below the England median for free school meals eligibility [19]. The randomisation will be conducted immediately after T1 baseline data is collected.

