## Statistical methods

### Statistical methods for primary and secondary outcomes {20a}

Baseline demographic characteristics for the participating schools will be summarised using means and 95% confidence intervals for continuous variables and frequencies and percentages for categorical variables. Contextual data such as %FSM eligibility, IMD and Public Health England data from National Child Measurement Programme (NCMP) [1] will be provided at school and Lower Super Output Area (LSOA) [20] levels respectively in a summary table.

Primary analysis of the effectiveness of the intervention on outcome data for the trial arms will be compared using two-way mixed analysis of variance (ANOVA) and multivariable regression models. The statistical analyses will be conducted using the following: food literacy score, cooking skills score and fruit and vegetable intake score as the dependent variables; time (T1 and T2) as the repeated measures independent variable; and treatment (intervention/control) as the independent groups variable. Effect size coefficients will be reported with measures of variation as well as Cohen’s *d* to determine the relative size of the effectiveness. We have identified the key outcomes on which we are basing our evaluation and any additional results will be interpreted cautiously and with the awareness that multiple testing is an issue. To reduce this risk, we will consider using statistical significance at the 1% level.

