### Methods for additional analyses (e.g. subgroup analyses) {20b}

Secondary analysis will use a theory-based approach to explore the interplay of mechanisms and context [10], including model fidelity. This will involve adjusting for pre-specified baseline school and child level covariates to investigate the impact of the intervention arm for individual clusters. Multiple regression will be used with the number of intervention components as a predictor variable. In addition, %FSM and IMD will be used in a linear model as predictor variables. The study will have low power to detect all but the largest differences in subgroups.

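### Randomisation is stratified by region and free-school-meal level, but the stated primary analysis uses neither factor; once school clustering is modelled, precision is lost to the extent that the strata are prognostic beyond baseline

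*Protocol article*

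**What the plan says.** Sequence generation {16a} describes blocked randomisation of schools, in which "schools will be stratified according to region (e.g. Selby or Harrogate) and whether they are above or below the England median" for free school meal eligibility. With two regions and two FSM levels that is up to four strata for 28 schools.

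The abstract then divides the covariates: "Primary analyses will adjust for baseline food literacy and cooking skills scores and secondary analysis will adjust for pre-specified baseline school and child level covariates".

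Section {20a} says that the arms will be "compared using two-way mixed analysis of variance (ANOVA) and multivariable regression models". The independent variables it names are "time (T1 and T2) as the repeated measures independent variable; and treatment (intervention/control) as the independent groups variable". It does not list the covariates of the regression models, and it names no school term.

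FSM returns in {20b}, among the additional analyses: "In addition, %FSM and IMD will be used in a linear model as predictor variables". There it is the percentage rather than the stratum used for randomisation. Region is not named in any analysis.

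Sample size {14} assumes a two-level model with children within schools, 15 children per school, 20% of variation at school level, 14 schools per arm recruited and an effect size of 0.52.

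**The concern.** Stratified randomisation forces the arms to be nearly balanced on region and FSM level, so differences between strata drop out of the treatment contrast. If the model has no term for the strata, those differences stay in its error variance. The reported standard error is then larger than the real sampling variation of the estimate. The test rejects less often than its nominal level, and the precision that stratification was meant to buy is not collected.

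With only 28 schools, variation between schools dominates the standard error, so a school-level factor that predicts outcome is worth having in the model. The protocol itself treats deprivation as relevant: it stratifies on FSM and lists %FSM and the index of multiple deprivation as covariables in its objectives.

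**Working it through.** The plan gives no figure for how much of the variation between schools the strata explain, so there is no stated result to reproduce. That share, f, is an assumption and is shown as a range.

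**Inputs from Sample size {14}:** ICC ρ = 0.20; children per school m = 15; schools per arm K = 14; d = 0.52 in units of the total SD. **Assumed:** two-sided α = 0.05 (the section states none); f from 0 to 0.40; outcome not yet adjusted for baseline.

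**Step 1. Variance of a school mean (total variance 1).**
- Strata ignored: V0 = ρ + (1 − ρ)/m = 0.20 + 0.80/15 = 0.2533
- Strata in the model: V1 = ρ(1 − f) + (1 − ρ)/m
- Example, f = 0.20: V1 = 0.16 + 0.0533 = 0.2133, a fall of 16%

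**Step 2. Standard error.** SE = √(2V/K). Ignoring the strata reports SE0 = √(2 × 0.2533/14) = 0.190. The real sampling SE under stratified allocation is SE1 = √(2V1/14). The overstatement is SE0/SE1 = √(V0/V1).

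**Step 3. Actual level of a nominal 5% test without strata.** 2[1 − Φ(1.96 × SE0/SE1)].

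**Step 4. Power at d = 0.52.** With strata: noncentral t on 24 df, noncentrality 0.52/SE1. Without strata: approximately Φ(0.52/SE1 − t × SE0/SE1), with t the 97.5% point on 26 df.

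| f | V1 | SE1 | SE0/SE1 | Actual level without strata | Power without strata | Power with strata |
|---|---|---|---|---|---|---|
| 0 | 0.2533 | 0.190 | 1.00 | 5.0% | 75% | 75% |
| 0.10 | 0.2333 | 0.183 | 1.04 | 4.1% | 76% | 78% |
| 0.20 | 0.2133 | 0.175 | 1.09 | 3.3% | 77% | 82% |
| 0.40 | 0.1733 | 0.157 | 1.21 | 1.8% | 79% | 89% |

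A simulation of 28 schools in four unequal strata (4,000 runs per setting) agrees in direction. Without strata, the level of a school-level analysis was 0.044, 0.040 and 0.028 at f = 0, 0.1 and 0.3. With strata it was 0.044, 0.048 and 0.054. Power went from 0.74 to 0.74, 0.77 to 0.79, and 0.78 to 0.86.

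**Step 5. The named terms taken literally, with no school effect.** The reported SE is √(2/(14 × 15)) = 0.098, against a real SE1 of 0.175 at f = 0.20. The level is 2[1 − Φ(1.96 × 0.0976/0.1746)] = 27%. Adding the strata alone lowers the residual variance to 1 − 0.20 × 0.20 = 0.96 and the reported SE to √(2 × 0.96/210) = 0.096, and the level becomes 28%. The strata therefore do not repair a model that lacks a school term.

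**Step 6. Effect of baseline.** Steps 1 to 4 apply f to the whole school-level variance. The primary analysis adjusts for baseline scores, and the mixed ANOVA compares change over time. Stable differences between strata cancel in change scores and are partly absorbed by baseline adjustment. Only stratum differences that remain after baseline count, so the lower rows of the table are more likely to overstate the gain.

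**The case against.** A reader might infer that the planned primary analysis has standard errors that are too large and is conservative. The documents do not support that as a flat statement. The terms named in {20a} include no school effect, and read literally that model errs the other way (Step 5). The conservative direction applies only once clustering is modelled, as the two-level model in {14} implies. Even then the loss is zero if the strata do not predict outcome, and the protocol gives no figure for this and does not say how the 28 schools will divide between strata. This objection stands and limits the claim.

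It can also be said that an article need not list every model term, and that the abstract does not say the primary analysis adjusts for baseline scores and nothing else. The regression covariates are indeed not itemised. But the abstract does more than stay silent: it allocates baseline scores to the primary analysis and school-level covariates to the secondary one, and {20b} places %FSM accordingly. An analysis plan that followed this division would leave both randomisation factors out of the primary model. The point about silence therefore fails for FSM. It has some force for region, which is simply not mentioned.

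Finally, omitting the strata does not bias the estimate, and in a clustered analysis the test stays valid. That is correct: the cost is precision only.

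**Conclusion.** The point holds in conditional form. The protocol randomises within strata of region and FSM level and, by its own division of covariates, leaves both out of the primary analysis. In an analysis that respects school clustering, this overstates the SE by 0 to 21% for an assumed 0 to 40% share of school-level variance, at ICC 0.20, 15 children per school and 14 schools per arm, before baseline adjustment. After baseline adjustment the gain from adding the strata is likely to be smaller. At a 20% share the overstatement is 9%, with about 5 points of power lost (77% against 82%).

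The change is worth making because it is nearly free even if the strata prove uninformative: at f = 0, power is 74.6% with them and 75.1% without. It also fixes the adjustment set in advance in a trial whose analyst, according to {17a}, cannot be blinded.

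The power figures here fall below the 90% planned in {14}. That is a separate question about the sample size calculation, and this point does not depend on it.

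**What to change.** State in {20a}, and bring the abstract into line, that the primary model for food literacy, cooking skills, and fruit and vegetable intake includes:

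- the baseline score;
- region and the FSM stratum, coded as used in the randomisation, as fixed effects;
- a school-level random effect, or an equivalent cluster-level analysis.

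Keep continuous %FSM, the index of multiple deprivation and the other school and child covariates for the secondary models. The school term must come with the strata, since the strata alone do not correct the SE.

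The cost is a short addition to the text and no new data. It uses about two of the 26 school-level degrees of freedom with two regions. It would use more if recruitment is widened geographically, as Trial design {8} allows, because region would then have further levels.
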